### Data collection

All study participants must weigh themselves once at the start of the study and at 1, 6, 12, and 24 months postpartum and track their activity and sleep patterns for 1 week at the beginning of the study and at 6, 12, and 24 months postpartum. Body weight will be measured once a day in the morning using the weight and body composition monitor. Activity and sleep will be measured using an activity and sleep tracker, which will be worn on the non-dominant arm at all times, even during sleep, except during recharging (once every 5 days).

All participants will complete online questionnaires at the beginning of the study and at 1, 6, and 12 months postpartum. If any data are lacking, they will be collected from the medical records. Details of the questionnaires developed for this study are as follows (supplementary file):

Background and lifestyle (at the start of the study): items related to pregnancy and delivery history, medical history, family history, and exercise and dietary habits.Edinburgh Postnatal Depression Score (EPDS) (start of study, 1 month postpartum) [22].Breastfeeding status (intensity, duration) questionnaire (1, 6, 12 months postpartum).Breastfeeding process questionnaire (1 month postpartum).Behavioral changes (attitude, knowledge) (6, 12 months postpartum).User-friendliness of devices, barriers to lifestyle improvements and behavioral changes, areas for improvement, etc. (6, 12 months postpartum) (both groups).Desire to continue using the IoT devices after the trial ends (12 months postpartum) (intervention group only).

All participants will have blood samples taken at home via postal self-checkups at 6, 12, and 24 months postpartum to measure HbA1c, fasting glucose, total protein, albumin, AST, ALT, γ-GTP, total cholesterol, HDL cholesterol, triglycerides, urea nitrogen, creatinine, and uric acid. To collect blood samples, the trial secretariat will send test kits to the participants for postal self-checkups. Results of the postal self-checkups will be returned by mail to the participants within 6 weeks.

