All participants will measure their blood pressure at home over 3 days at 6, 12, and 24 months postpartum. The HBF-227t sphygmomanometer manufactured by OMRON Healthcare Co. will be used. Measurements will be taken twice a day in the morning (within 1 h of waking up, after urinating, before taking any medication, and after resting for 1–2 min) and before going to sleep (after resting in the sitting position for 1–2 min). In principle, two measurements will be taken each time.

Table 1 shows the schedule for the trial.

**Table 1 Tab1:** Study timeline for intervention and data collection

		Trial duration								
		Obtain consent		Intervention						Completion
Pregnancy, postpartum			Start of trial	During pregnancy	Delivery	1 month postpartum	6 weeks postpartum	6 months postpartum	12 months postpartum	24 months postpartum
	Obtain consent	×								
	Registration	×								
Regular management	Regular medical care, guidance (maternity checkups)Regular health guidance			○ (maternity checkup→→		○ (1-month postpartum checkup)				
Measure at home	Weight, body composition		○			○		○	○	○
	Activity, sleep		○					○	○	○
Blood pressure	Blood Pressure							○	○	○
Postal checkups	Postal checkup (blood glucose, HbA1c, etc.)							○	○	○
App intervention	Weight, activity, sleep		●	→→→→→→→			●→→→	→→→→→→	→	
	Meal photos		●	→→→→→→→			●→→→	→→→→→→	→	
Mother and Child Handbook	Maternity checkup data (urine test, blood pressure, weight)					○				
	Pregnancy outcome data					○				
Questionnaire	Background, lifestyle		○							
	EPDS		○			○				
	Breastfeeding status					○		○	○	
	Breastfeeding process					○				
	Behavioral changes (attitude, knowledge)		○					○	○	
	User-friendliness of devices							○	○	
	Desire to continue using IoT after end of study								●	

○ Both groups, ● intervention group only

If there are missing data, the research coordinator at each site and trial secretariat will contact the participants. Data from the weight and body composition monitor, activity and sleep tracker, and online questionnaires will be stored on the Internet server. The data file will be secured with a password, and access to information will be limited to designated members such as the researchers and the trial secretariat. Paper-based documents such as consent forms will be stored at each site.

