#### Health outcomes

✓ Pregnancy outcomes (gestational age at delivery, cesarean section rate, preterm birth rate, excessively large baby rate, birth height, birth weight, SD value, large-for-gestational-age rate, pregnancy-induced hypertension rate, gestational diabetes rate, etc.)Maternity checkup and pregnancy outcome data will be collected from the Maternal and Child Health Handbook.✓ Weight gain during pregnancy (kg)Calculated as: (weight immediately before delivery retrieved from the Maternal and Child Health Handbook)—(pre-pregnancy weight).✓ Change in weight from before pregnancy to 1, 6, 12, and 24 months postpartum (kg)✓ Rate of change in weight from before pregnancy to 1, 12, and 24 months postpartum (%)

The postpartum weights will be directly retrieved from the smartphone application as measured by the device.✓ Percentage of participants who will reach the target weight (at 6, 12, and 24 months postpartum) (%)A participant will be considered to have reached the postpartum target weight if/when their body weight declines to 93% of the weight before pregnancy.✓ Change in body fat ratio from 1 month postpartum to 6, 12, and 24 months postpartum✓ Percentage of participants with hypertension (excluding those having been diagnosed before pregnancy)The mean of the two blood pressure readings taken at home in the morning and before going to bed will be used. If only one blood pressure reading is taken, that value will be used. Hypertension is defined as a 3-day mean of ≥ 135 mmHg and/or ≥ 85 mmHg.✓ Percentage of participants with impaired glucose tolerance or diabetes (at 6, 12, and 24 months postpartum)Postpartum impaired glucose tolerance is defined as fasting blood glucose ≥ 110 mg/dl and ≤ 125 mg/dl or HbA1c ≥ 6.0% and ≤ 6.4% in the at-home blood samples. Diabetes is defined as a fasting blood glucose level of ≥ 126 mg/dl or HbA1c is ≥ 6.5%.✓ Percentage of participants with EPDS ≥ 9 (start of the study and at 1 month postpartum)

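### Postpartum hypertension and glucose outcomes use measured values only, so a woman treated since delivery whose values fall below the cut-offs is counted as not having the condition

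*Protocol article*

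**What the plan says.** Under Health outcomes, the protocol article gives complete case rules for two postpartum conditions, which Table 2 schedules at 6, 12 and 24 months.

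- **Hypertension.** "Hypertension is defined as a 3-day mean of ≥ 135 mmHg and/or ≥ 85 mmHg". The section also says what to do when only one reading is available. Its sole exclusion is in the outcome label: "Percentage of participants with hypertension (excluding those having been diagnosed before pregnancy".
- **Glucose.** "Postpartum impaired glucose tolerance is defined as fasting blood glucose ≥ 110 mg/dl and ≤ 125 mg/dl or HbA1c ≥ 6.0% and ≤ 6.4" per cent, from the home sample. "Diabetes is defined as a fasting blood glucose level of ≥ 126 mg/dl or HbA1c is ≥ 6.5" per cent. The two are reported together as one proportion.

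Data collection describes the measurements. "All participants will measure their blood pressure at home over 3 days at 6, 12, and 24 months postpartum". The morning reading is to be taken "before taking any medication". For blood tests, "All participants will have blood samples taken at home via postal self-checkups at 6, 12, and 24 months postpartum", and "Results of the postal self-checkups will be returned by mail to the participants within 6 weeks".

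The same section asks about medical history at study start only. The topics listed for 6 and 12 months are breastfeeding, behavioural change, device usability and, in the intervention group at 12 months, the wish to continue. Table 1 schedules no questionnaire at 24 months. Medical records are named as the source for data that are lacking.

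**The concern.** Blood pressure, glucose and HbA1c are the quantities that treatment lowers. If case status rests on them alone, a woman who developed hypertension or diabetes and is controlled on medication is indistinguishable from one who never had it. The reported proportion then mixes occurrence of disease with success of treatment.

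The hypertension rule makes this visible. It uses a past diagnosis to remove women from the denominator but ignores current treatment when counting cases. Under Analysis of secondary outcomes, proportions are compared between groups by a chi-square test, so the misclassification passes directly into the reported comparison at each time point.

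**Working it through.** **Step 1. Which women are misclassified.** Applying the printed rules to a woman treated with medication since delivery:

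| Her measured values | Hypertension outcome | Combined glucose outcome |
|---|---|---|
| Still at or above the hypertension or diabetes cut-off | Case | Case |
| Intermediate glucose (110–125 mg/dl) or HbA1c (6.0–6.4%) | not applicable | Case, as impaired glucose tolerance |
| Below all cut-offs | Not a case | Not a case |

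Only the last row is a problem.

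**Step 2. How treatment could come about.**
- *Glucose.* Results are mailed within 6 weeks (about 1.4 months). A 6-month result can thus reach a woman about 6 − 1.4 = 4.6 months before the 12-month test, and a 12-month result about 12 − 1.4 = 10.6 months before the 24-month test. No mailed result precedes the 6-month test.
- *Hypertension.* The mailing covers blood tests only. The routes are usual care and the woman's own home readings.

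**Step 3. Whether any described data source would catch it.** Medical history is asked once, at the start. The listed 6- and 12-month topics contain no medication item, and 24 months has no questionnaire. Medical records fill lacking values, but a treated woman with a normal reading has no value lacking.

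**Step 4. Effect on the comparison.** The documents state no rate, difference or power for these outcomes, so there is no plan figure to reproduce for them. All rates below are assumptions.

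The number per arm comes from Sample size: 226 in total, hence 113 per arm. That total itself reproduces. With a difference of 3 points, SD 8, two-sided 5% and 80% power, n = 2 × (1.960 + 0.842)² × 8² / 3² = 111.6, rounded up to 112 per arm (224). The noncentral t calculation gives 113 per arm (226, power 0.801).

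Let p be the true proportion and u the share of cases treated to below the cut-offs. Then observed proportion = p × (1 − u).

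*Equal u in both arms, true rates 20% (control) and 10% (intervention), 113 per arm:*

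| u | Observed control | Observed intervention | Difference (points) | Power (two-proportion test) |
|---|---|---|---|---|
| 0% | 20% | 10% | 10 | about 56% |
| 10% | 18% | 9% | 9 | about 51% |
| 30% | 14% | 7% | 7 | about 40% |
| 50% | 10% | 5% | 5 | about 30% |

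The absolute difference shrinks by the factor 1 − u. The ratio of the two rates stays at 0.5, because 1 − u cancels.

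*Unequal u, true rates 15% in both arms:*
- Control u = 10%: 15% × 0.9 = 13.5%. Intervention u = 30%: 15% × 0.7 = 10.5%. This is a false benefit of 3 points.
- The reverse split gives a false harm of 3 points.
- Any equal u gives no false difference.

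For scale, the standard error of 13.5% minus 10.5% at 113 per arm is √(0.135 × 0.865/113 + 0.105 × 0.895/113) = 0.043. The false difference is thus below one standard error.

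**The case against.** **The omission may be only apparent.** The article summarises the questionnaires and refers to a supplementary file that is not shown, so a medication item may exist. That stands as far as data collection goes. It does not rescue the outcome: the case rules are printed in full, down to the handling of single readings, and would not use such an item.

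**The problem may be rare.** Women with diabetes before pregnancy or overt diabetes in pregnancy are excluded at entry (Participants), and no incidence or treatment rate is given. This stands. A reader might infer that the mailed results make misclassification likely for both outcomes. The documents support only a possibility, for glucose alone, and only at 12 and 24 months.

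**The medication wording is a timing instruction.** A reader might take it as proof that treated women are expected in the analysed group. It applies to all participants, including those with pre-pregnancy hypertension, whom this outcome excludes. It therefore shows nothing about treated cases among those analysed. Reading before the morning dose can reduce masking in part, but the bedtime reading has no such condition.

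**Both arms get the same tests and feedback.** A reader might infer that the comparison is biased in favour of one arm. That needs unequal treatment uptake. Participants are unblinded and only one arm receives continuing personalised advice, so unequal uptake is conceivable, but nothing in the documents shows it. Without it, the effect is under-counting and lost power in secondary outcomes for which no power is claimed.

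**Conclusion.** The point holds as a defect in a stated outcome definition. Women on treatment begun since delivery whose values are below every cut-off are counted as non-cases. Treated women who remain in the hypertensive, diabetic or impaired range are still counted.

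If any such women exist, the proportions are too low. With equal uptake the absolute group difference is also attenuated where a true difference exists. A shift in either direction requires unequal uptake.

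The size cannot be derived from the documents; the percentages under the working are illustrations on assumed inputs. The primary outcome and its sample size are untouched. The change is worth making because it is cheap and because control of the condition by drugs should not be read as its absence.

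**What to change.** In Health outcomes, define a case at each of 6, 12 and 24 months as a woman who **either** meets the measured threshold **or** currently takes antihypertensive medication (hypertension outcome) or glucose-lowering medication (combined glucose outcome) started since delivery or continued beyond it. Keep the exclusion of hypertension diagnosed before pregnancy. Keep pregnancy-induced hypertension and gestational diabetes as separate pregnancy outcomes. Report the measured-only definition as a sensitivity analysis.

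Base the added clause on current medication, not on any diagnosis since study entry. Entry is before 30 weeks of gestation, so a diagnosis clause would carry resolved pregnancy conditions into the postpartum outcome. It would also keep a woman a case permanently, even if her values became normal through weight loss.

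Collect the information with one yes/no current-medication item per condition in the 6- and 12-month online questionnaires, and a short item sent with the 24-month postal test. The medical-record back-up cannot replace this, since it covers lacking data only.

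The cost is one definition sentence, two yes/no items in existing questionnaires and one short addition at 24 months. Self-reported medication will carry some error.

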### Secondary outcomes

The following items will be evaluated (shown in Table 2):

**Table 2 Tab2:** Primary and secondary outcomes

Outcomes				Trial duration							
					Intervention						Finished
				Registration	During pregnancy	Delivery	1 montha postpartum	6 weeks postpartum	6 months postpartum	12 months postpartum	24 months postpartum
Primary			Rate of change in body weight from before pregnancy to 12 months postpartum	×						×	
Secondary	Health outcomes	Bothgroup	Pregnancy outcomes (cesarean section rate, preterm birth rate, LGA rate, excessively large baby rate, pregnancy-induced hypertension rate, gestational diabetes rate, etc.)			×					
			Rate of change in body weight from before pregnancy	×			×		×		×
			Percentage who reached the weight target						×	×	×
			Body fat ratio				×		×	×	×
			Hypertension rate						×	×	×
			Impaired glucose tolerance rate						×	×	×
			Edinburgh Postnatal Depression Score ≥9 rate	×			×				
	Behavioral changes		Number of steps	×					×	×	×
			Sleep	×					×	×	×
			Attitude, knowledge	×					×	×	
			Breastfeeding rate				×		×	×	
			Breastfeeding process				×				
		Intervention group only	Percentage of carbohydrates, fat, protein, dietary fiber in diet	×					×	×	
	Use of IoT/mobile app		Rate of use of weight-body composition monitor, activity-sleep tracker	×					×	×	
			Number of logins to mobile app, browsing time	×					×	×	
			Meal image/content upload status	×					×	×	
			Intervention program continuation rate						×	×	
			Adherence	×					×	×	×
			Desire to continue using IoT after end of study	×						×	
		Bothgroup	User-friendliness of the devices	×					×	×	

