### Sample size

Assuming a -2% weight change at 12 months postpartum compared to before pregnancy in the non-intervention group, the trial was designed to detect whether the IoT/mobile application intervention would result in a -5% weight change at 12 months postpartum. To conduct a two-sided test with a standard deviation of 8% and significance level of 5% at 80% power, 226 participants in both groups are needed. Assuming loss of approximately 20% of participants from exclusion or drop-out, the target number of registrations is set to 270 women.

There are 6,000 deliveries each year at the trial institutions. If 10% of the women are obese, the total number comes to 600 per year. As pregnant women at up to 30 weeks of gestation are eligible for registration, 250 pregnant women at up to 30 weeks of gestation who have already visited the outpatient maternity clinic for checkups and 250 pregnant women who newly visit during the 5-month registration period will be eligible. Hence, it is expected to be possible to register the target number of participants.

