### Analysis of secondary outcomes

For continuous variables, the mean and 95% confidence interval will be calculated for each group and t-tests will be used for group comparisons. For discrete variables, the number, proportion, and 95% confidence interval for the proportion will be calculated for each group, and the chi-square test will be used for group comparisons.

Regarding the breastfeeding proportion, ≥ 80% breastfeeding (daily milk amount ≤ 125 ml at 1 month postpartum and ≤ 164 ml at 6 months postpartum) will be used for between-group comparisons. Regarding the dietary items, the means and 95% confidence intervals will be calculated for each item at each time point (at the start of the study and 6 and 12 months postpartum) in the intervention group. The same analysis will be performed to analyze changes from the start of the study to 6 and 12 months postpartum.

For device usage, the use of activity tracker meters, wearing the weight/body composition monitor, and performance of measurements with the weight/body composition monitor at each time point (6 and 12 months postpartum) will be summarized and compared between the groups. In the group that will not use the devices at the beginning of the study, the number, proportion, and 95% confidence interval for the proportion will be calculated for participants who started using the devices at 6 and 12 months postpartum.

Regarding mobile application use, the mean and 95% confidence intervals will be calculated for the number of logins and viewing time at each time point in the intervention group (at 6 and 12 months postpartum). For uploading of meal images (at 6 and 12 months postpartum) and viewing of breastfeeding videos (during pregnancy and at 6 weeks postpartum), the number, proportion, and 95% confidence interval will be calculated for the intervention group.

Regarding the continuation of the intervention program (at 6 and 12 months postpartum), the number, proportion, and 95% confidence interval will be calculated for the intervention group.

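### The full EPDS score is collected in both arms, but the only mental-health outcome listed is the proportion at 9 or more; a score comparison at 1 month should be added beside it.

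*Protocol article*

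**What the plan says.** Four places in the protocol article settle the point.

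- **Data collection** has all participants complete the questionnaire twice: "Edinburgh Postnatal Depression Score (EPDS) (start of study, 1 month postpartum".
- **Health outcomes** turns it into a dichotomy: "Percentage of participants with EPDS ≥ 9 (start of the study and at 1 month postpartum". **Table 2** (Secondary outcomes) does the same: "Edinburgh Postnatal Depression Score ≥9 rate". Neither lists a mean score or a change in score, and no other mental-health outcome appears.
- **Analysis of secondary outcomes** says of discrete variables that "the chi-square test will be used for group comparisons".
- The same section has a rule for continuous outcomes, which the EPDS score never reaches: "For continuous variables, the mean and 95% confidence interval will be calculated for each group and t-tests will be used for group comparisons".

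Subgroup analysis names the EPDS without a cut-off, but only in a list of endpoints already defined elsewhere. It does not create a score outcome. The article gives no expected share at or above 9, no EPDS standard deviation, no target difference and no EPDS power.

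**The concern.** The score exists in both arms at both times, and its planned use keeps only the side of 9 on which each woman falls. A woman who moves from 3 to 8, or from 10 to 18, counts as unchanged. No reason is given for dropping the rest. Body weight, by contrast, is reported as kilograms, as a percentage change and as a target-reached rate.

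The intervention combines a weight target of 93% of pre-pregnancy weight with daily self-monitoring and automated advice. The Monitoring section dispenses with a data monitoring committee, and the Harms section presumes that the intervention does no harm. The EPDS comparison is therefore the only listed between-group evidence on depressive symptoms, whether the effect is a benefit or a harm. If that comparison is imprecise, a non-significant result could be read as reassurance that the data cannot give.

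**Working it through.** **Inputs from the document (Sample size).** The design assumption is "Assuming a -2% weight change at 12 months postpartum compared to before pregnancy in the non-intervention group", against -5% with the intervention, so the difference is 3 points. The other settings are "To conduct a two-sided test with a standard deviation of 8% and significance level of 5% at 80% power" and "226 participants in both groups are needed".

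**Assumptions, not in the document.** Allocation is 1:1 (113 per arm) with independent observations. The score is roughly normal and shifts as a whole between arms. The control share p at EPDS 9 or more is taken as 10% to 30%, with 50% as the most favourable case for the cut. The shift d = 3/8 = 0.375 SD is borrowed from the weight outcome purely as a yardstick.

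**Step 1. Reproduce the plan's own figure.** n per arm = 2 × (1.960 + 0.842)² × (8/3)² = 111.6, which rounds up to 112, or 224 in total. The t-test version gives 112.6, so 113 per arm and 226 in total. The stated figure reproduces.

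**Step 2. Information kept by the cut.** For a small shift, the efficiency of the proportion relative to the mean is φ(c)² / [p(1 − p)], where c is the upper-p normal quantile. At p = 20%: c = 0.8416, φ(c) = 0.2800, and 0.0784 / 0.16 = 0.49. So 226 women analysed on the cut carry the information of about 226 × 0.49 ≈ 111 women analysed on the score.

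**Step 3. Power on the score.** Φ(0.375 / √(2/113) − 1.960) = Φ(2.819 − 1.960) = Φ(0.859) = 80%.

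**Step 4. Power on the proportion.** The other arm's share is p₁ = 1 − Φ(c ± 0.375), with plus for improvement and minus for worsening. Power = Φ[(|p − p₁| − 1.960 × SE₀) / SE₁], with SE₀ pooled and SE₁ unpooled. At p = 20%, improvement: p₁ = 1 − Φ(1.217) = 11.2%, SE₀ = 0.0483, SE₁ = 0.0479, and Φ[(0.0881 − 0.0946) / 0.0479] = Φ(−0.136) = 45%.

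| Assumed share ≥ 9 | Efficiency | Information lost | Improvement: share, power | Worsening: share, power |
|---|---|---|---|---|
| 10% | 0.34 | 66% | 4.9%, 31% | 18.2%, 43% |
| 15% | 0.43 | 57% | 7.9%, 39% | 25.4%, 50% |
| 20% | 0.49 | 51% | 11.2%, 45% | 32.0%, 54% |
| 30% | 0.58 | 42% | 18.4%, 53% | 44.1%, 59% |
| 50% | 0.64 | 36% | 35.4%, 60% | 64.6%, 60% |

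Against 80% on the score, the shortfall at shares of 10% to 30% is about 28 to 50 points for improvement and 21 to 38 points for worsening. The loss falls to 40% at a share of about 34% and reaches its minimum of 36% at 50%.

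**Step 5. Other shift sizes, 20% share, 113 per arm.**

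| Shift (SD) | Score | Proportion: worsening / improvement |
|---|---|---|
| 0.2 | 32% | 19% / 17% |
| 0.3 | 62% | 37% / 32% |
| 0.375 | 80% | 54% / 45% |
| 0.5 | 96% | 80% / 65% |

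**Step 6. Skewed scores.** A simulation with negative-binomial scores (control shares 12% to 31%, mean raised by 30% or lowered by 25%, 113 per arm) gave 55% to 85% power for the t-test and 36% to 66% for chi-square. Case by case the gap was 17 to 23 points, so the advantage of the score does not depend on normality, though its size does.

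**The case against.** The strongest reply is that nothing here is contradictory. The EPDS is one of many secondary outcomes, and a threshold is how this plan treats health conditions generally: hypertension and impaired glucose tolerance are also measured on a scale and listed only as rates. That is fair. It makes the cut a consistent convention rather than a slip, and it supports keeping the proportion. It does not explain why the score goes unused when the plan already has a rule for continuous outcomes.

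Three stronger readings are tempting, and the document supports none of them.

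- **A reader might infer that more than 40% of the information is lost, whatever the data.** That needs a share at or above 9 below about 34%, plus a normal-shift model. The share is not given; at 35% to 50% the loss is 36% to 40%.
- **A reader might infer that an effect in either direction would probably be missed.** That depends on the effect size, and 0.375 SD is a weight effect that nothing ties to the EPDS. A worsening of that size is picked up slightly more often than not from a 20% share upward, and a 0.5 SD worsening has 80% power at that share. At 0.2 SD the score itself has only 32%. The 113 per arm is also the 12-month requirement. If all 270 registered women supplied a 1-month score (135 per arm), the proportion would have 51% to 62% power at a 20% share, against 87% on the score.
- **A reader might infer that the proportion should give way to the score.** A mean difference can miss a change confined to the upper tail, which is where a harm might lie. The two summaries answer different questions.

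One could add that this is a condensed article and that a score analysis may be planned elsewhere. The point still stands on what is stated: the outcome is defined twice, both times as a rate.

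**Conclusion.** The concern holds in a limited form. The plan lists a weaker analysis of data that it already collects in full. The loss is at least about 36% of the score's information under a normal shift, and 42% to 66% if 30% down to 10% of women score 9 or more. At an illustrative 0.375 SD with 113 per arm, power is about 80% on the score, against 31% to 53% (improvement) or 43% to 59% (worsening) on the proportion. These figures rest on an assumed share, an assumed 1:1 split and a borrowed effect size. The direction of the conclusion survives a skewed score; the exact sizes do not. The trial is not sized for the EPDS under either analysis, and the primary weight analysis is untouched. This is a worthwhile improvement to a secondary outcome, not a flaw in the trial's main conclusion.

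**What to change.** Add one line to the Health outcomes list and to Table 2: EPDS total score at 1 month postpartum, compared between groups as a mean difference with 95% CI, adjusted for the start-of-study score. The adjustment goes one step beyond the plan's t-test rule for continuous variables but uses a value already collected. Keep the proportion at 9 or more, with its chi-square comparison, as the clinical case definition, and report the two together. State that neither comparison was powered, so that a wide interval is not read as evidence of no effect.

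The cost is one more secondary analysis, with no new data and no added burden on participants. It does add one more test to an already long list of secondary outcomes, so the estimate and its interval should carry the interpretation.
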